## Assignment of interventions: blinding

### Who will be blinded {17a}

Due to the design of the intervention, i.e., decision coaching with the decision aid, blinding is not possible, as the participants in the control group realize easily that they are not part of the intervention as they get no decision coaching and vice versa.

### Procedure for unblinding if needed {17b}

Since blinding is impossible (see above) there is no unblinding procedure.

## Data collection and management

### Plans for assessment and collection of outcomes {18a}

#### Primary outcome

The *Decisional Conflict Scale (DCS)* [16] was developed to operationalize the quality of medical decisions. It measures the uncertainty about which choice is the right one to make. The five dimensions are uncertainty, level of information, values clarity, social support, and effective decision.

For analysis, the authors recommend six sum scores: one for each of the five dimensions and one for an overall value. As the test construction assumes that the five subscales are predictors for the overall value, it is reasonable and in line with measurement theory to choose the subscale value clarity as the single primary outcome.

Both test-retest reliability (*r* ≥ .81) and internal consistency (Cronbach’s *α* ≥ .78) for all subscales are satisfactory. Cronbach’s *α* for the subscale values clarity is .91. Item selectivity and sensitivity for change are assumed to be satisfactory (effect sizes between 0.4 and 1.2) [16]. The DCS correlates with other constructs that are relevant for decision-making, e.g., decision regret, knowledge, or change of treatment decision. The German version of the DCS shows comparable values concerning internal consistency and correlations between subscales [17].

#### Secondary outcomes

The *Decision Self-Efficacy Scale (DSES)* [18] is based on Bandura’s concept of self-efficacy [24] and measures the perceived ability to engage in treatment-related behaviors and decisions. Cohen’s *α* is .84 and the scale discriminates adequately between patients who want to continue their treatment vs. patients that are unsure or prefer to delay the decision.

The *Preparation for Decision-Making Scale (PDMS)* is designed to assess the extent to which individuals feel prepared to make a medical decision with the help of supportive materials [25]. Preparation for decision-making is defined as “a patient’s perception of how useful a decision aid or other decision support intervention is in preparing the respondent to communicate with their practitioner at a consultation visit and making a health decision.” The Scale shows high internal consistency (*α* = .92) [25].

Results on the concurrent validity of the German version PDMS-D correspond with previous international study findings [26]. Individuals who felt well prepared reported lower decision uncertainty and less lack of information or social support, or ambiguity of personal values (subscales of the DCS) [19, 25].

The *Perceived Involvement in Care Scale (PICS)* is designed to examine the factors of doctor facilitation of patient involvement, level of information exchange, and patient participation in decision-making. All three subscales show good internal consistency (Cronbach’s α = .65–.87) [27].

In regard to construct validity, the subscales “patient activation by physicians” and “active information behavior of the patient” are highly correlated with satisfaction. The correlation of “active-information-behavior-of-the-patient” with satisfaction is positive but non-significant, which may be due to cultural differences in the healthcare systems in the US vs. Germany [20]. German patients tend to adhere to a paternalistic model and apparently expect stronger guidance from their physicians and tend to take less responsibility for medical decisions.

The *EQ-5D-5L* is an instrument for describing and valuing health. It defines health in 5 dimensions: mobility, self-care, usual activities, pain/discomfort, and anxiety/depression. The test-retest reliability (Cohens Kappa and/or ICC) and convergent validity for different patient populations have been shown to be good [28].

The *Hospital Anxiety and Depression Scale (HADS)* was designed to identify and quantify the two most common forms of psychological disturbances in medical patients, namely anxiety and depression. The Cronbach’s alpha and split-half reliabilities for both subscales of the HADS are .8 each. The HADS and its translations have been extensively validated [23, 29].

### Plans to promote participant retention and complete follow-up {18b}

Participants may withdraw from the study for any reason at any time. A drop-out rate of approximately 20% is expected. To keep drop-out at a minimal level, patients are reminded by a phone call to fill in the questionnaires and bring them to their next appointment.

### Data management {19}

The questionnaires will be checked for completeness and entered by qualified study personnel in the statistical analysis system. After data entry (according to the code book) a data quality check on plausibility will be performed. All questionnaires completed as part of the study will be digitized, archived at the Thoraxklinik after completion of the study, and retained for ten years. For the survey, patients are given a pseudonym. Only the study director has access to the pseudonym list of respondents. Only the digitized data will be shared for analysis. These electronic data are archived after completion and deleted after ten years.

### Confidentiality {27}

Only investigators will have access to study-related patient information. Personal information and confidentiality of data entry, coding, security, and storage are in line with the German privacy protection law (Bundesdatenschutzgesetz, BDSG) [30] and the privacy policy of the University Hospital Heidelberg.

All questionnaires completed as part of the study will be digitized, archived at Thoraxklinik after completion of the study, and retained for 10 years. For the survey, patients are given a pseudonym. Only the study director has access to the pseudonym list of respondents. Only the digitized data will be shared for analysis. These electronic data are archived after completion of the evaluation and deleted after 10 years.

### Plans for collection, laboratory evaluation, and storage of biological specimens for genetic or molecular analysis in this trial/future use {33}

As there will be no biological specimens collected there are no plans for laboratory evaluation and/or storage.

## Statistical methods

### Statistical methods for primary and secondary outcomes {20a}

A descriptive analysis of all collected patient information and data (as well as the scales that can be formed from the instruments) is performed: mean, standard deviation, median, minimum, and maximum, for continuous variables and absolute and relative frequencies for categorical variables.

For all (primary and secondary) analyses, the intervention arm (HELP intervention: decision coaching and decision aid) will be compared against the control arm (standard care/decision situation). The primary outcome measure is the sum score of the clarity of personal attitude dimension of the Decisional Conflict Scale (DCS). In addition to the descriptive evaluation, it will be analyzed by group comparisons (non-parametric comparison: van Elteren test) between the two study groups in which the stratification of randomization is considered.

For the sum scores and scales of the secondary outcomes, group comparisons (taking stratification into account) are also performed in order to detect significant differences. Depending on the group, the Cochran-Mantel-Haenszel test, the van Elteren test, or an analysis of covariance are used.

Results are reported along with descriptive *p*-values and 95% confidence intervals. *P*-values will be reported to four decimal places with *p*-values less than 0,05 considered statistically significant. Analysis is performed using statistical software SPSS (version 27, IBM) or R (version 4.0. http://r-pro-ject.org) (Table 2).

**Table 2 Tab2:** Variables, measures, and methods of analysis

Variable/outcome	Hypothesis	Outcome measure	Methods of analysis
**1) Primary**	Intervention improved outcome in comparison to the control group		
Clarity of personal attitude/values clarity		Values clarity subscore of Decisional Conflict Scale (DCS-D)	van-Elteren-test

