#### Control group

The participants in the control group get usual care, i.e., the doctor-patient conversation takes place without preliminary coaching and deliberation about their preferences and goals.

Before the consultation with their physician, participants fill in the pre-survey questionnaires (Decisional Conflict Scale, Decision Self-Efficacy Scale, EQ 5D, Hospital Anxiety and Depression Scale). After the consultation, the post-survey questionnaires are handed out or mailed to them (Patient Involvement in Care Scale, EQ-5D, Hospital Anxiety and Depression Scale).

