**2) Secondary**			
Decisional certainty	Improvement in comparison to control	Uncertainty subscore of Decisional Conflict Scale (DCS-D)	Cochran-Mantel-Haenszel test/ van-Elteren-test
Decisional support	Improvement in comparison to control	Support subscore of Decisional Conflict Scale (DCS-D)	Cochran-Mantel-Haenszel test/ van-Elteren-test
Being informed	Improvement in comparison to control	Informed subscore of Decisional Conflict Scale (DCS-D)	Cochran-Mantel-Haenszel test/ van-Elteren-test
Decision Effectiveness	Improvement in comparison to control	Effective decision subscore of Decisional Conflict Scale (DCS-D)	Cochran-Mantel-Haenszel test/ van-Elteren-test
Decreased decisional conflict	Improvement in comparison to control	Decisional Conflict Scale (DCS-D) – total score	Cochran-Mantel-Haenszel test/ van-Elteren-test
Self-efficacy	Improvement in comparison to control	Decisional Self-Efficacy Scale (DSES)	Cochran-Mantel-Haenszel test/ van-Elteren-test
Patient involvement in decision	Improvement in comparison to control	PDM subscore of Perceived Involvement in Care Scale (PICS-D)	Cochran-Mantel-Haenszel test/ van-Elteren-test
Information seeking	Improvement in comparison to control	PI subscore of Perceived Involvement in Care Scale (PICS-D)	Cochran-Mantel-Haenszel test/ van-Elteren-test
Health care provider facilitation	Improvement in comparison to control	HCP-FAC subscore of Perceived Involvement in Care Scale (PICS-D)	Cochran-Mantel-Haenszel test/ van-Elteren-test
Quality of life	Improvement in comparison to control	EQ5D-5L	Cochran-Mantel-Haenszel test/ van-Elteren-test
Emotional well-being	Improvement in comparison to control	Hospital Anxiety and Depression Scale (HADS-D)	Cochran-Mantel-Haenszel test/ van-Elteren-test

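### Section {20a} calls p-values descriptive yet labels any p below 0.05 significant, without separating the single primary test from the 11 secondary comparisons

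*Protocol article*

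**What the plan says.** All the relevant text is in the Protocol article.

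- **Status of the p-values.** Section {20a}: "Results are reported along with descriptive" p-values and 95% confidence intervals.
- **Decision rule.** The following sentence sets the number of decimal places and then treats p-values "less than 0,05 considered statistically significant". It does not say to which outcomes this applies.
- **Purpose of the secondary tests.** Earlier in {20a}, for the secondary sum scores and scales, "group comparisons (taking stratification into account) are also performed in order to detect significant differences".
- **Number of secondary tests.** Table 2, block 2, has 11 rows: four Decisional Conflict Scale (DCS) subscores and the DCS total score ("Decreased decisional conflict"), the self-efficacy scale, three subscores of the involvement scale, EQ-5D-5L and HADS-D. Each carries the hypothesis "Improvement in comparison to control".
- **What is marked exploratory.** Only the preparation scale (PDMS-D, intervention group only) is labelled explorative and given a descriptive analysis.
- **Primary outcome.** Sections {12}, {18a} and {20a} name one primary outcome, the values clarity subscore, with one test (van Elteren). Section {14} ties the two-sided 5% level and the 80% power to that outcome.

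**The concern.** A descriptive p-value is reported without a verdict attached. A p-value with a 0.05 threshold and the word significant is a test result. Section {20a} asks for both, for the same p-values. Read literally, the descriptive label even covers the primary test, which {14} plans as a formal two-sided 5% test. The significance rule, in turn, covers all 11 secondary comparisons.

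The authors had an exploratory label to hand and used it for PDMS-D, but not for these 11 rows. Nothing in the text makes a secondary claim depend on the primary result. If values clarity showed no difference, the written rule would still allow a significance claim on any of 11 other patient-reported outcomes, with no control of the error rate across them. What is at stake is how the secondary results are interpreted and reported. The main conclusion of the trial is not at risk from this.

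**Working it through.** **1. The plan's own figure.** The article states no familywise error rate. Its only error-rate calculation is the sample size in {14}, which concerns the primary outcome: difference 10, SD 20.6, two-sided 5%, power 80%.

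- Normal-theory size per group: 2 × (20.6 × (1.960 + 0.842) / 10)² = 66.6.
- Multiplied by π/3 for the Mann-Whitney test: 69.8, so 70. The plan gives 71.
- Simulated Mann-Whitney power at 71 per group with normal data (20,000 runs): 79.9%.
- Dropout: 71 / (1 − 0.20) = 88.75, so 89 per group and 178 in total, as stated.

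The figure reproduces. It uses the full 5% for one test, which is consistent with a single primary outcome.

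**2. Count of secondary comparisons.** From Table 2, block 2: 5 (DCS) + 1 (self-efficacy) + 3 (involvement) + 1 (EQ-5D-5L) + 1 (HADS-D) = 11.

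**3. Chance of at least one p<0.05 if no secondary effect exists.**

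- Independent tests: 1 − 0.95^11 = 0.431.
- Expected number of false positives: 11 × 0.05 = 0.55.
- Correlated tests: the article gives no correlations, so these are assumed. Test statistics were simulated as Z_j = √ρ × C + √(1 − ρ) × E_j, with C and E_j standard normal, 200,000 draws, counting draws in which any |Z_j| exceeds 1.96.

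| Assumed pairwise correlation | Any p<0.05 among 11 | Any p<0.05 favouring the intervention |
|---|---|---|
| 0 | 43% | 24% |
| 0.3 | 37% | 19% |
| 0.5 | 30% | 15% |
| 0.7 | 22% | 11% |

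The favourable-only figure under independence is 1 − 0.975^11 = 0.243.

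**4. A more structured assumption.** Five of the 11 rows come from the DCS, and one of these is its total. With within-scale correlations of 0.4 to 0.6, between-scale correlations of 0.1 to 0.3 and the DCS total built from its subscales, the chance of any p<0.05 is 32% to 38%, and of one favouring the intervention 16% to 20%. This lies inside the range in the table.

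**The case against.** The strongest reply is that the confirmatory structure is sound. There is one prespecified primary outcome with one named test, alpha and sample size are tied to it alone, and no interim analysis is planned ({21b}). Unadjusted secondary tests beside a single primary are common, and the article already calls its p-values descriptive and pairs them with confidence intervals. The 0.05 phrase sits in a sentence about decimal places and could be a mere labelling convention. All of this stands as regards the primary result. It does not remove the conflict, because the label is attached to every p-value and the secondary tests are given the stated purpose of finding significance. This is also not a matter left to an analysis plan: the article states a rule, and the rule contradicts itself.

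A reader might go further in four ways that the document does not support.

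- *That a chance secondary claim is likely.* For the 11 listed rows the probability stays below one half even under independence, which is the least plausible case given the shared instrument. The rule would call a result significant only if p<0.05; it does not call every comparison significant.
- *That the number of tests is really larger.* EQ-5D and HADS are collected before the consultation and again with the later set ("After the consultation, the post-survey questionnaires are handed out or mailed to them"). Testing EQ-5D and two HADS subscales at both times would give 15 tests and 1 − 0.95^15 = 54% under independence. Table 2 has one row for each instrument and does not say that both times will be tested. The choice of time point is detail that an article may leave to the full protocol or analysis plan.
- *That the per-protocol repeat adds materially to the risk.* It is listed as a sensitivity analysis, on the same outcomes and a subset of the same patients, so it adds little independent chance of error.
- *That a formal adjustment is required.* A Holm procedure after a significant primary result is one option if secondary claims are wanted. It is a preference, and clear labelling is enough.

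**Conclusion.** The point holds as an internal contradiction in a stated rule. Section {20a} gives the same p-values a descriptive status and a significance threshold, and does not separate the one primary test from 11 secondary comparisons for which no hierarchy or adjustment is stated. If no secondary effect exists, the chance of at least one nominally significant secondary result is about 22% to 43%, roughly 4 to 9 times the nominal 5%, and about half of that would be in favour of the intervention. These figures rest on the count of 11 from Table 2, two-sided tests at 5%, no true effect on any secondary outcome, and assumed correlations from 0 to 0.7. They do not bear on the primary test, which keeps its 5% level, or on the sample size. The matter is worth correcting before analysis, but it is confined to the interpretation of the secondary results.

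**What to change.** Amend section {20a} in four places:

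1. State that the van Elteren test of the values clarity subscore is the only confirmatory test, at a two-sided 5% level.
2. Limit the 0.05 significance rule to that test.
3. In the sentence on the secondary scores, delete the clause that gives detection of significant differences as the purpose.
4. State that secondary and per-protocol results are reported as estimates with 95% confidence intervals and descriptive p-values, without significance wording.

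This costs a few words and needs no further patients, data or analyses. The small downside is that individual secondary results can no longer be labelled significant.

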**2) Secondary**			
Decisional certainty	Improvement in comparison to control	Uncertainty subscore of Decisional Conflict Scale (DCS-D)	Cochran-Mantel-Haenszel test/ van-Elteren-test
Decisional support	Improvement in comparison to control	Support subscore of Decisional Conflict Scale (DCS-D)	Cochran-Mantel-Haenszel test/ van-Elteren-test
Being informed	Improvement in comparison to control	Informed subscore of Decisional Conflict Scale (DCS-D)	Cochran-Mantel-Haenszel test/ van-Elteren-test
Decision Effectiveness	Improvement in comparison to control	Effective decision subscore of Decisional Conflict Scale (DCS-D)	Cochran-Mantel-Haenszel test/ van-Elteren-test
Decreased decisional conflict	Improvement in comparison to control	Decisional Conflict Scale (DCS-D) – total score	Cochran-Mantel-Haenszel test/ van-Elteren-test
Self-efficacy	Improvement in comparison to control	Decisional Self-Efficacy Scale (DSES)	Cochran-Mantel-Haenszel test/ van-Elteren-test
Patient involvement in decision	Improvement in comparison to control	PDM subscore of Perceived Involvement in Care Scale (PICS-D)	Cochran-Mantel-Haenszel test/ van-Elteren-test
Information seeking	Improvement in comparison to control	PI subscore of Perceived Involvement in Care Scale (PICS-D)	Cochran-Mantel-Haenszel test/ van-Elteren-test
Health care provider facilitation	Improvement in comparison to control	HCP-FAC subscore of Perceived Involvement in Care Scale (PICS-D)	Cochran-Mantel-Haenszel test/ van-Elteren-test
Quality of life	Improvement in comparison to control	EQ5D-5L	Cochran-Mantel-Haenszel test/ van-Elteren-test
Emotional well-being	Improvement in comparison to control	Hospital Anxiety and Depression Scale (HADS-D)	Cochran-Mantel-Haenszel test/ van-Elteren-test
**3) Subgroup analyses**			
*Additional analysis IG*			
Preparation for decision	(Explorative approach)	Preparation for Decision Making Scale (PDMS-D)	Descriptive
**4) Sensitivity analyses**			
Per protocol analysis	Improvement in comparison to control	All outcomes	

### Interim analyses {21b}

No interim analyses will be performed.

### Methods for additional analyses (e.g., subgroup analyses) {20b}

The adjustment for the variable of decision-making type (used in the stratified randomization) is already considered with the application of the van-Elteren-test in the primary analysis of the outcome. There are no subgroup analyses planned.

### Methods in analysis to handle protocol non-adherence and any statistical methods to handle missing data {20c}

#### Analysis population

As analysis populations, the two common populations of intention-to-treat and per-protocol are defined and used. The intention-to-treat population considers all patients as randomized regardless of whether they finished the whole survey procedure. Criteria for determining the per-protocol population are as follows: patients who stayed in their randomized group, answered the first questionnaire before the decision-making (and for IG: after the intervention), and answered the second questionnaire within the timeframe of 1–4 weeks after the treatment decision.

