### Trial design {8}

The HELP-study is designed as a randomized, controlled, open monocenter, two-arm superiority trial with two parallel groups and a primary endpoint of “clarity of personal attitude” as operationalized by the Decisional Conflict Scale (DCS) which will be collected before the decision event. Following the assumptions that the HELP intervention strengthens patient autonomy and their clarity of personal values in relation to the treatment decision, the described design of the two-arm, parallel goups, superiority trials was chosen. Since it can be assumed that the effect of the HELP intervention will differ depending on the participant’s decision style, stratified randomization according to the decision type was chosen in order to take this aspect into account in the group comparisons of the outcome analyses. Therefore, randomization will be performed as stratified block randomization according to the characteristic of preferred decision-making at baseline with a 1:1 allocation.

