##### Decision coaching

The coaching takes place in person or, if necessary, by telephone or online. The coaching process follows the sections of the HELP decision aid: patient’s information needs, the preferred method of decision-making, and the clarification of central personal values.

After the coaching session and before the consultation with the physician, participants fill in the questionnaires (Decisional Conflict Scale, Decision Self-Efficacy Scale, Preparation for Decision Making Scale, EQ 5D, Hospital Anxiety and Depression Scale) before their consultation with the physician. After the consultation, the post-survey questionnaires are handed out or mailed to participants (Patient Involvement in Care Scale, EQ-5D, Hospital Anxiety and Depression Scale).

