### Participant timeline {13}

Participation in the study includes the completion of two questionnaires for each participant (before and after the medical consultation at intervals of 1–4 weeks). The questionnaires will be handed over personally (including a stamped return envelope) or sent by e-mail. The time needed to answer the questionnaires is about 10 min.

In addition to the questionnaire survey, the application of the decision aid incl. decision coaching will be carried out with participants in the intervention group. This can take place, depending on the patient’s wishes, either in the clinic or at another location, by telephone or by video conference. The time frame is about 30–45 min for the decision aid and the accompanying conversation. Appointments are made in person, by phone, or by mail.

The total study-related time required is therefore about 20 min for persons who participate exclusively in the questionnaire survey and about 50 to a maximum of 65 min for persons who are invited both to the questionnaire survey and to the decision coaching (Figs. 1 and 2).

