**Fig. 1 Fig1:**
[figure not shown]
Schedule of enrolment, interventions, events, and assessments (SPIRIT figure). ** Timepoint: t_3_= consultation with physician (decision making), −t_1_ and t_0_ = 6–8 days before physician consultation, t_1_ and t_2_ = 2–5 days before physician consultation, t_4_ = 1–14 days after physician consultation

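### The per-protocol window for the second questionnaire does not match the Fig. 1 schedule, and the one per-protocol set also filters the pre-consultation primary outcome on that later form

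*Protocol article*

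**What the plan says.** Four places in the protocol article bear on this.

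- **Analysis population (item 20c).** The per-protocol set has one definition: the patient stayed in the randomised group, answered the first questionnaire before the decision (in the intervention arm, also after the intervention), and "answered the second questionnaire within the timeframe of 1–4 weeks after the treatment decision".
- **Fig. 1 legend.** Timepoint t3 is the "consultation with physician (decision making"), so the consultation and the decision are the same event. Timepoint t4 is "1–14 days after physician consultation". Timepoints t1 and t2 are "2–5 days before physician consultation".
- **Participant timeline (item 13).** The two questionnaires are completed "before and after the medical consultation at intervals of 1–4 weeks".
- **Table 2, sensitivity analyses.** The entry "Per protocol analysis" covers all outcomes, with no separate definition by outcome.

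The primary outcome is the values clarity subscore of the Decisional Conflict Scale (DCS), "which will be collected before the decision event" (Trial design, item 8). The second questionnaire does not contain the DCS: "After the consultation, the post-survey questionnaires are handed out or mailed to participants (Patient Involvement in Care Scale, EQ-5D, Hospital Anxiety and Depression Scale"). The Control group section lists the same three instruments after the consultation.

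**The concern.** A per-protocol set should pick out the patients who followed the protocol. Here the criterion and the figure legend count from the same event but give different windows, so some patients who keep to Fig. 1 fail the criterion and some who miss it pass.

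The second problem remains whichever window is right. A patient who stayed in the allocated arm, received coaching where allocated, and gave a valid DCS in time is removed from the per-protocol comparison of the primary outcome if a later form comes back at the wrong time or not at all. That form says nothing about the DCS. Whether it comes back can depend on what happens after the DCS is measured. The article itself foresees patients whose health declines until they cannot answer (item 11b) and questionnaires not returned after the consultation (Missing data, item 20c).

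At stake is how useful the per-protocol analysis is as a check on the primary result: valid observations are lost, and the remaining set may be selected on events after the outcome.

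**Working it through.** **Windows in days.** Both count from the consultation, which Fig. 1 equates with the decision. I read 1–4 weeks as days 7–28.

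| Day of answer | Fig. 1 (days 1–14) | Per-protocol (days 7–28) |
|---|---|---|
| 1–6 | on schedule | excluded |
| 7–14 | on schedule | included |
| 15–28 | off schedule | included |

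Six of the 14 scheduled days fall outside the per-protocol window: 6/14 = 43%. This is a share of days, not of patients.

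**Does the Participant timeline settle it?** It could mean the gap between the two questionnaires. With the first at t1/t2 (2–5 days before) and the second at t4 (1–14 days after), the gap runs from 2 + 1 = 3 to 5 + 14 = 19 days, which is not 7–28. The body of Fig. 1 is not available to me, so placing the first questionnaire at t1/t2 is an assumption; in the intervention arm it follows from completion after the coaching. In any case the per-protocol criterion counts from the treatment decision, not from the first questionnaire, so this wording does not reconcile the other two.

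**The plan's own sample size.** Inputs from Sample size (item 14): difference 10, SD 20.6, two-sided 5%, power 80%, Mann-Whitney test.

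- Normal approximation: n = 2 × [20.6 × (1.960 + 0.842)/10]² = 66.6 per group.
- Dividing by the Mann-Whitney efficiency 3/π = 0.955 gives 69.8. Adding the small-sample term 1.960²/4 = 0.96 before dividing gives 70.8, so 71.
- Simulated Mann-Whitney power with normal data (20,000 runs) was 0.799 at 70 and 0.793 at 71 per group, equal within simulation error.
- Dropout: 71/0.80 = 88.75, so 89 per group and 178 in total.

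The stated figures are reproduced.

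**Illustrative loss from the per-protocol comparison of the primary outcome.** With k patients left per arm, approximate power = Φ(10 / [20.6 × √(2/(k × 3/π))] − 1.960).

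| Lost | k per arm | Power for 10 points |
|---|---|---|
| 0% | 71 | 0.81 |
| 10% | 63.9 | 0.77 |
| 25% | 53.2 | 0.69 |
| 43% | 40.6 | 0.57 |

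The approximation gives 0.81 at 71 per arm and the simulation 0.79, so the starting point is about 0.80. The loss percentages are assumptions. The 43% row holds only if every patient answers on days 1–14 with returns spread evenly over them.

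**The case against.** **The criterion agrees with part of the article.** The Participant timeline also says 1–4 weeks, so the per-protocol rule echoes one of two scheduling statements. This stands: the schedule is itself inconsistent, and it would be wrong to say that the criterion simply departs from it. A reader might also infer that patients who follow the schedule are excluded as a class. The text supports this only for answers on days 1–6.

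**Issue and answer may be different things.** The second questionnaire is handed out or mailed, and t4 might mark its issue rather than its completion. Issue within 14 days and answering at 1–4 weeks could then coexist. The legend does not say, so this cannot be excluded, but it would itself have to be written down. A loose reading of the criterion as no later than 4 weeks would rescue days 1–6, but the text states a lower bound of one week.

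**The loss may be small.** Mailing, return envelopes and reminders to bring forms to the next appointment make later returns plausible, and returns on days 15–28 count as per protocol. This stands, and is why a range is shown.

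**Bias is not shown.** The rule is the same in both arms. Bias in the DCS comparison would need return behaviour to be related to both arm and DCS. The patients dropped by the window mismatch are prompt responders, not those who deteriorate. This also stands: selection is a risk, and the documents give neither direction nor size.

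**One per-protocol set requiring all assessments is common, and lower power is expected in a sensitivity analysis.** Both are true. Neither is a reason to discard a valid primary-outcome value because of a form that does not carry that outcome.

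**Conclusion.** The point holds, limited to the per-protocol sensitivity analysis. Three statements of the second questionnaire's timing do not agree. Taken literally, the per-protocol rule excludes on-schedule answers on days 1–6 and admits off-schedule answers on days 15–28. Independently of that, the primary outcome and the other outcomes on the first questionnaire are filtered on a later form. For PICS and the post-consultation EQ-5D and HADS, requiring that form is reasonable.

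The size is unknown. Power of about 0.77 to 0.57 corresponds to assumed losses of 10% to 43% from 71 per arm; the documents support no single value in that range.

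A reader might go further and infer that the per-protocol analysis is biased and worthless as a check, or that power will fall to about 0.57. The documents support neither: no differential return by arm is shown, and 0.57 rests on one assumed return pattern. Nor is the per-protocol analysis the only robustness check, since a separate sensitivity analysis for missing data is planned (Missing data, item 20c). The intention-to-treat definition and the sample size are untouched.

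**What to change.** 1. Reconcile the Participant timeline, the Fig. 1 legend and the Analysis population section to one post-consultation window. Say whether it refers to issue or to completion of the form. Let the per-protocol set accept every second questionnaire returned within it.
2. For outcomes on the first questionnaire (values clarity, the other DCS scores, DSES, pre-consultation EQ-5D and HADS), define per protocol by three conditions: randomised group retained, coaching received (intervention arm), and first questionnaire answered before the consultation.
3. Require the second questionnaire, within the agreed window, only for PICS and the post-consultation EQ-5D and HADS.

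The analysis change costs only wording. Recruitment, the intervention and the sample size stay as they are. If reconciling the window changes when patients are asked to answer, the instructions to patients and staff must follow. The drawback is that the per-protocol set then differs between outcomes, so its size must be reported by arm for each.
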